## Abstract

**Background:**

Late adolescence is a highly challenging and potentially critical period for young people with attention deficit hyperactivity disorder (ADHD). Many of the conditions that frequently co-occur with ADHD, such as depression, often first emerge in adolescence. Major life transitions, such as moving out of the parental home, lead to multiple new demands and changes in available support networks, further increasing the vulnerability. Additionally, UK data show that most young people with ADHD do not successfully transfer to adult services and thus do not receive appropriate interventions at a time when they may need them most. The lack of well-defined targets for holistic interventions limits opportunities for intervention. Our project on ADHD transition - ADHD Remote Technology and ADHD Transition: predicting and preventing negative outcomes (ART-transition) - uses remote measurement technology (RMT), which offers the potential to obtain ongoing, long-term, real-world data. We aim to identify the nature and timing of real-world changes in the transition to adulthood and what predicts such changes. We will further use these timeframes and intervention targets to co-design, with young people with ADHD, a prototype for an ADHD transition interactive smartphone app.

**Methods:**

ART-transition is a prospective cohort study that will recruit 250 16-17-year-olds with ADHD. The participants will complete baseline assessments, including an ADHD clinical interview, questionnaires, and cognitive tasks. Participants will then be monitored remotely over 24 months. Passive monitoring, which involves the participants wearing a wrist-worn device (Fitbit Charge 6) and downloading the study Passive App on their smartphone, will provide ongoing data collection on a range of variables, such as physical activity, sleep, heart rate, smartphone usage including social connectivity, and the environment (e.g. ambient noise, relative location). Active remote monitoring involves the participant downloading the study Active App to complete tasks (such as clinical questionnaires and speech tasks) and using a PC/laptop to complete cognitive tasks. The ADHD Remote Technology (ART) system is built on the RADAR-base mobile-health platform.

**Discussion:**

ART-transition will use RMT to identify fluctuations in ADHD symptoms and the wider phenotype at a level of detail not previously possible and to identify real-world targets for intervention.

**Clinical trial number:**

Not applicable.

**Supplementary Information:**

The online version contains supplementary material available at 10.1186/s12888-025-07546-0.

## Background

Late adolescence and the transition to adulthood is a highly challenging period for young people with attention deficit hyperactivity disorder (ADHD) that can lay the foundations for diverging adulthood trajectories. Many of the conditions that frequently co-occur with ADHD, such as depression, delinquency and substance misuse, often emerge in adolescence [1–3]. Major life transitions at this age, such as leaving education, starting work or moving out of the parental home, lead to multiple new demands and changes in available support networks, further increasing the vulnerability of young people with ADHD. This vulnerable phase coincides with the clinical transition from child and adolescent mental health care to adult services, which itself is a focus of major current clinical concern: UK data show that a large proportion of young people with ADHD do not successfully transfer to adult services, despite significant needs for ongoing treatment [4].

While people with ADHD are, at a group level, at an increased risk for outcomes such as educational underachievement, unemployment, and the development of many co-occurring psychiatric and physical disorders [5], individual long-term trajectories can be highly variable. Evidence for such variability in individual trajectories is emerging both for the development of comorbid conditions [6, 7] and the severity of ADHD symptoms and impairment [8]. Data from the Multimodal Treatment of ADHD study (MTA) challenge past notions of long-term ADHD trajectories by showing that for most of the sample (64%), the follow-up period from childhood to young adulthood was characterised by *fluctuating* ADHD persistence and remission; only 11% demonstrated stable persistence across all time points, and 9% sustained remission [8]. These data suggest that ADHD, though linked to a biological vulnerability, is a condition that may fluctuate over time in symptoms and impairment more than previously acknowledged, likely in response to environmental factors or health behaviours. The identification of such modifiable factors, which may serve as targets for new environmental or health interventions, emerges as a research priority. Overall, we lack detailed data on the extent to which ADHD and co-occurring symptoms fluctuate in late adolescence, what predicts improvement, worsening, or the emergence of new symptoms, and how such changes in clinical symptoms and functioning relate to other changes occurring during this period.

Past research has identified only limited clinical, cognitive and socio-economic predictors of the persistence of ADHD symptoms and functional impairment over time, such as ADHD severity, presence of co-occurring psychiatric symptoms (e.g. depression, oppositional problems), lower general cognitive ability, low SES and male gender [9–12]. The narrow range of predictors assessed and the long assessment intervals of several years mean that such data are of limited use for understanding the changes taking place during the ADHD transition phase. Potentially promising data on modifiable lifestyle factors has come from research on physical activity [13–19]. For example, in a longitudinal population-based study of 232 identical twin pairs, greater energy expenditure at age 16–17 predicted reduced ADHD symptoms at age 19–20, even after adjusting for unmeasured confounding using a within-identical twins design [16]. The evidence from RCTs for ADHD medication as a predictor of improvement in clinical symptoms in the short term is strong [20], but we need data on a wider range of longer-term outcomes during ADHD transition. Most acutely, treatment non-adherence is exceedingly common during ADHD transition, yet is poorly understood [17]. Data from UK primary care suggest only 18% of young people prescribed medication for ADHD in their early teens continued to receive prescriptions beyond the age of 18 [21]. Even when receiving prescriptions, individuals often do not take their medication regularly. We need to better understand the reasons for treatment non-adherence among young people with ADHD and establish if treatment adherence, jointly with lifestyle factors such as physical activity, predicts optimal functioning. The available limited data suggest that the presence of some comorbidities, such as affective disorders and autism, may increase the likelihood of continued treatment during transition; yet other data link autism to a more difficult transition [22].

Remote measurement technology (RMT) offers unprecedented opportunities for addressing current research and clinical challenges. For longitudinal research on ADHD, RMT enables us to move from infrequent ‘snapshot’ assessments in artificial lab or clinic settings on modest sample sizes, to frequent or ongoing, long-term, real-world data collection on a wide range of novel as well as conventional measures, in large, geographically representative samples. For the current project on ADHD transition, RMT offers the potential to both identify fluctuations in symptoms and the wider phenotype at a level of detail not previously possible, and to identify real-world targets for intervention that include environmental factors and health behaviours. The project benefits from our ADHD Remote Technology (ART) remote monitoring system for adolescents (ages 16+) and adults with ADHD, which we have previously successfully applied in our ART pilot study [23–26] and our ongoing ‘ART-CARMA’ project on adults with ADHD (ADHD Remote Technology study of cardiometabolic risk factors and medication adherence [27]). ART consists of both active (questionnaires, cognitive tasks, speech task) and passive (e.g. physical activity, sleep, smartphone use and sensor data) monitoring using mobile and web technologies. The measures are collected via the RADAR-base mobile-health platform [28], previously applied to other disorders, such as depression [29]. The ART pilot study provided support for the acceptability, feasibility and validity of the approach and measures [23–26]. Using a within-individual design allows us to control for many potential confounders [30], while regularised multivariable prediction models will allow us to capture complex temporal relationships between a range of measures and ADHD outcomes.

ADHD is diagnosed, through clinical interview, when an individual exceeds a threshold for symptoms of inattention and/or hyperactivity-impulsivity, and if the symptoms cause significant functional impairment. A challenge during the transition phase to adulthood is that the main informant for ADHD diagnostic symptoms changes from parent (and teacher) to self; yet data show that agreement between parents and young people with ADHD is only modest [31]. While self-report of symptoms and functional impairment has, necessarily, validity for clinical decision-making, the limited agreement between parents and young people with ADHD highlights the importance of extending the measurement of symptoms and impairments to objective digital and cognitive markers, which can further contribute to an improved understanding of the underlying processes.

Promising digital signals for other disorders have emerged from studies such as Remote Assessment of Disease and Relapse – Major Depressive Disorder (RADAR-MDD), where worsening depression was linked, for example, to over-time changes in speech collected using a study Active App [32] and a reduced nearby Bluetooth device count as a proxy for social isolation [33]. The latter emerged from the RADAR-base Passive App, which collects ongoing data from the smartphone sensors on novel digital markers ranging from smartphone-use behaviours (e.g. sociability, app usage) to background data such as relative location, ambient noise and light. In the ART pilot study, using Active and Passive App data collected from 40 participants with and without ADHD over a 10-week remote monitoring period, we identified candidate ADHD digital signals of restlessness, inconsistent attention, and difficulties completing tasks [23]. While cognitive tasks allow well-established measurement of cognitive differences associated with ADHD, past longitudinal studies are limited to a few (often just two) time points [7, 34–38]: we do not know whether changes in cognitive functioning are stable or fluctuate over time. In ART-pilot we developed and validated self-administration versions of two ADHD-sensitive cognitive tasks, enabling repeated assessment over time [24]. Our past studies further suggest a link between attention dysregulation and arousal dysregulation in people with ADHD [39, 40]. Wearable technology now enables us to move the measurement of, for example, heart rate from the lab to the real world. Overall, the long-term, ongoing RMT real-world data collection in the current project provides an opportunity to assess a wide range of detailed candidate objective markers of clinical symptom severity, in addition to the Active App being used to obtain self-ratings and the web-based Research Electronic Data Capture (REDCap) web-based platform to obtain informant-ratings on clinical questionnaires.

The discovery of genome-wide significant risk loci for ADHD enables us to derive a polygenic score (PGS) for each individual that captures the genetic signal underlying ADHD [41]. ADHD PRS is associated with many co-occurring psychiatric traits [42, 43], as well as with attention regulation in people with ADHD measured with tasks comparable to those applied in the present study [38]. We will thus account for ADHD genetic risk in ART-transition by incorporating an ADHD PGS. Capturing its contribution even in more modestly sized samples will bring added value.

### Participant involvement in the ART‑transition study protocol

The ART system benefits from feedback from participants in the ART-pilot feasibility study on the acceptability of the chosen measures and procedures [25]. Of the participants in ART-pilot, 95% agreed that there is value in gathering data through RMT, with some participants explaining that passive monitoring provides a unique opportunity to collect objective data. All participants agreed that the study measures blended into their daily lives, and 82% of participants expressed positive views about using the system for at least one year. The ART-transition study further benefits from the service user focus group for the ADHD Remote Technology study of cardiometabolic risk factors and medication adherence (ART-CARMA) study, which uses the ART system in adults with ADHD. The feedback from the ART-CARMA focus groups informed this study design regarding the frequency of questionnaire administration and the acceptability of measures.

In preparation for using the ART system with young people (aged 16+), we conducted several focus groups with young people. The groups included a Young Persons’ Mental Health Advisory Group session (*n* = 8), young people with ADHD who had recently transitioned from child and adolescent mental health services (CAMHS) to adult ADHD services (*n* = 10), and two young people with ADHD and a parent of a young person with ADHD (*N* = 3). In these groups, participants described the transition as a difficult process. They also viewed the development of an ADHD transition app positively and made suggestions on potential components. We also gained feedback on adapting our “About You” demographics questionnaire for young people, an ADHD symptom daily symptom question, and the participant and summary information sheets. Feedback from all the focus group sessions has been incorporated into the study design. Lastly, we have set up a patient and public involvement (PPI) panel (*N* = 7) to provide feedback throughout the study on areas such as recruitment, debrief interviews, participant feedback, and interpreting the results.

### Study objectives

This project, ADHD Remote Technology and ADHD transition: predicting and preventing negative outcomes (ART-transition), will use RMT in adolescents with ADHD to collect unobtrusive, real-world data over 24 months. By recruiting 250 16-17-year-olds with ADHD and monitoring them remotely, we can address the following three main aims: Aim 1) To identify, with precision, the nature and timing of the real-world changes that take place in the transition to adulthood; Aim 2) To identify what predicts such changes; and Aim 3) To use the timeframes and intervention targets identified in Aims 1–2 to co-design, with young people with ADHD, a prototype for a new ADHD-transition interactive smartphone app.

Aim 1 incorporates five objectives: To identify changes in (1a) ADHD symptoms and functional impairment; (1b) new co-occurring psychiatric symptoms that may emerge (e.g. anxiety, depression, irritability, substance use, antisocial behaviour); (1c) treatment adherence and engagement with clinical services; and (1d) healthy lifestyle behaviours (e.g. physical activity, sleep, daily structure, online lifestyle), social support and employment/ studies; and (1e) To identify objective markers – digital signals and cognitive measures – that are associated with changes in the clinical symptoms. Aim 2 focuses on the development and validation of multivariable prediction models for each of the changes (outcomes) identified in Aim 1, incorporating four objectives: To identify factors that predict changes in (2a) ADHD symptoms and functional impairment; (2b) co-occurring symptoms; (2c) treatment adherence and engagement with clinical services; and (2d) adoption of healthy lifestyle behaviours and engagement with work/studies. Information on influential predictors and their timing will feed directly into Aim 3 of developing a prototype ADHD-transition smartphone app.

## Method

### Study design

ART-transition is a prospective, observational, non-randomised, non-interventional study that uses wearable technology and smartphone sensors to remotely monitor 250 16–17-year-olds with ADHD for 24 months. The study does not represent any change to participants’ usual care or treatments due to participation. There is no control comparison group or randomised group allocation.

### Study population

The sample sizes were determined by simulation and analytical methods. For Aim 1, we considered power to detect associations between pairs of variables (e.g., ADHD symptoms and digital markers), provide precise of estimates of within-person variance and intraclass correlation (ICC), and the impact of missing data. For Aim 2, we estimated the sample size needed to develop multivariable prediction models (based on an expected model performance of R² ≈ 0.5 and 20 model parameters). Full details are provided in the Supplementary Materials. Overall, a sample of 250 participants (each providing monthly outcome assessments and continuous RMT data collection) will be sufficient to detect associations and estimate within-person variance with precision (Aim 1), even under conservative assumptions about missing data. This sample will be adequate to develop multivariable prediction models. Table 1 summarises the study eligibility criteria.

**Table 1 Tab1:** Eligibility criteria for participation in ART-transition

Participant inclusion criteria	1	Diagnosis of DSM-5 ADHD
	2	Aged 16–17
	3	Able to give informed consent for participation
	4	Willing and able to complete self-reported assessments via smartphone
	5	Willing to use either their own compatible Android phone or a study Android phone as their only smartphone during the data collection period
	6	Willing to wear the wearable device (Fitbit) during the data collection period
Participant exclusion criteria	1	Psychosis, currently experiencing a major depressive episode, mania, drug dependence in the last six months, or a major neurological disorder
	2	Recent contact with psychiatric acute care (admission, crisis team or liaison team (A&E)) in the last six months
	3	Any other major medical disease which might impact upon the patient’s ability to participate in normal daily activities (e.g., due to hospitalisations)
	4	Pregnancy
	5	IQ < 70
Informant inclusion criteria	1	A parent or guardian, as chosen by the participant with ADHD
	2	Aged 18 or over
	3	Willing and able to complete web-based questionnaires regarding the participant with ADHD

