Recruitment through clinical and private CAMHS teams involves the clinical teams contacting relevant individuals by their preferred method of contact (post, email, or telephone) and providing them with information about the study. If they consent for their details to be passed onto the research team, the research team will contact the patient and provide them with further information. If the patient is interested in participating, the first baseline assessment with the research team will be scheduled.

The baseline assessments take approximately four hours to complete across two days, with approximately a week between sessions. The virtual baseline sessions consist of (1) the Diagnostic Interview for ADHD in Adults (DIVA [45] to have a record of current ADHD symptoms and clinical impairment (2), a brief IQ and short-term working memory test [46, 47] (3) two baseline questionnaires: a demographic About You questionnaire and the Autism Spectrum Quotient questionnaire (AQ-10 [48]), (4) two cognitive tasks of the Combined Cued Continuous Performance Test and Go/NoGo (CPT/GNG) task and the Fast Task (while researcher present) [24], (5) completion of questionnaires (see Table 2) (6), a training session on the smartphone and wearable device, and (7) guidance on how to collect DNA saliva sample (optional). Participants are able to take breaks during the sessions if required. During the baseline sessions, the participants are also asked to identify a partner, a family member or a close friend who could complete informant report versions of the active monitoring questionnaires on ADHD symptoms, impairment, and irritability. The participants are asked to forward an email to their chosen informant, which asks the informant to get in touch with the research team if they are happy to participate. If the informant consents to participation, they will be sent online questionnaires using the REDCap web-based platform.

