Participants are asked to report their medication use side effects weekly using the CADDRA Patient ADHD Medication form [49]. This form contains four items on changes experienced since starting medication and 28 items on side effects. Every four weeks, participants are asked to complete a longer set of questionnaires: ADHD symptoms and impairments will be measured using the Barkley Adult ADHD Rating scale on current symptoms (BAARS-IV) [50] and Barkley ADHD functional impairment scale [51]. This includes the 18 diagnostic ADHD symptoms and 10 items on functional impairment. Depression is measured using the 8-item Personal Health Questionnaire Depression Scale (PHQ-8 [52]), which is a widely used measure of current depression in the general population; anxiety is measured using the 7-item Generalized Anxiety Disorder questionnaire (GAD-7 [53]), which provides a dimensional score of anxiety symptoms; aggression is measured using the 23-item Reactive-Proactive Aggression Questionnaire for Adults (RPQ-A [54]); irritability is measured using the self-reported 7-item Affective Reactivity Index questionnaire (ARI-s [55]); smoking behaviours are measured using the 6-item Test Fagerstrom questionnaire [56]; and alcohol use is measured using the Alcohol Use Disorders Identification Test (AUDIT [57]). In addition, participants are asked to complete a remote monitoring version of the “About you” questionnaire, which includes questions on changes to life circumstances, life events, medication use, and other ADHD-related and non-ADHD-related treatments. Every six months, participants are asked to complete two further questionnaires. Positive and negative feelings about the self are measured using the 10-item Rosenberg Self-Esteem Scale [58], and eating disorder symptoms are measured using the 12-item Eating Disorder Examination Questionnaire (EDE-QS) [59].

Participants are asked to complete a short speech task every four weeks on the Active App. They also self-administer the two cognitive tasks of CPT/GNG and Fast task four times during the 24 months (months 6, 12, 18, and 24) on their home PC or laptop, without the researcher present. In addition, ratings on ADHD symptoms are obtained monthly from a partner, a family member, or a close friend of the individual with ADHD using the web-based REDCap.

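### Table 1 admits only a parent or guardian aged 18 or over as informant, but the procedures recruit partners, relatives and close friends, so informant scores may mix rater types across participants

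*Protocol article*

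**What the plan says.** The protocol article defines the informant in three places.

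- **Study population, Table 1 (informant inclusion criteria).** The first criterion is "A parent or guardian, as chosen by the participant with ADHD" and the second is "Aged 18 or over". The third is willingness and ability to complete the web questionnaires.
- **Study procedures.** At the baseline sessions "participants are also asked to identify a partner, a family member or a close friend who could complete informant report versions" of the ADHD, impairment and irritability questionnaires. "The participants are asked to forward an email to their chosen informant", and an informant who consents receives the questionnaires through REDCap.
- **Remote data collection, Active app.** During follow-up, "ratings on ADHD symptoms are obtained monthly from a partner, a family member, or a close friend of the individual with ADHD".

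Table 2 schedules two informant instruments at baseline and every month to month 24: the BAARS-IV with the functional impairment scale, and the ARI. Participants are 16 or 17 at entry.

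**The concern.** The eligibility table and the two procedural sections define different groups of people, and staff who follow one will breach the other. Two separate sections carry the wider list, so it is unlikely to be a single slip of the pen.

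Two things are at stake. The first is eligibility. Partners and friends of 16- and 17-year-olds may themselves be under 18, and the sections that recruit them do not mention the age limit. The second is measurement. If some participants are rated by a parent and others by a partner or friend, a difference in informant score between two participants may reflect who did the rating as well as how severe the symptoms are. Objectives 1a and 1b name ADHD symptoms, functional impairment and irritability, which are the constructs the informant scales measure.

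**Working it through.** The plan states no figure on this point, so the check is mainly a comparison of the texts.

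**Step 1. Set the two rules side by side.**

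| Candidate informant | Table 1 | Study procedures and Active app |
|---|---|---|
| Parent, 18 or over | Eligible | Invited, as family |
| Guardian who is a relative, 18 or over | Eligible | Invited, as family |
| Guardian who is not a relative, 18 or over | Eligible | Not on the list |
| Other relative who is not a guardian, 18 or over | Not eligible | Invited |
| Partner or close friend, 18 or over | Not eligible | Invited |
| Partner, close friend or sibling under 18 | Not eligible, on relationship and on age | Invited; no age limit repeated |

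The rules agree only on parents and on guardians who are relatives. They disagree in both directions elsewhere, so neither list is contained in the other.

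**Step 2. Can they be read together?** One could treat the procedures as describing whom the participant may suggest, with Table 1 then screening the suggestion. Every partner and friend would then be turned away, and naming them would serve no purpose. The Active app sentence also does not fit this reading, because it says who supplies the monthly ratings and not who may be considered. The age limit is different. The procedures omit it but do not contradict it, so informants under 18 are a possibility only if staff work from the procedures alone.

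**Step 3. Which data are exposed?** Table 2 gives one informant occasion at baseline and one in each of months 1 to 24, so 1 + 24 = 25 per participant. If all 250 participants had an informant, 250 × 25 = 6,250 informant reports would be scheduled. That is an upper limit, because taking part is the informant's choice. How many would come from someone other than a parent or guardian cannot be derived.

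**Step 4. What does mixing do to the scores?** Write the informant score of participant i at month t as

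Y(i,t) = severity(i,t) + b(i) + error(i,t),

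where b(i) is the offset of the type of rater that participant has.

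- *Between persons.* The participant's mean score contains mean severity plus b(i). With two rater types, a share p of the second type and a difference d between types, the offset adds p(1 − p)d² to the between-person variance. If the choice of rater is related to severity, it also adds a covariance term that can bias comparisons in either direction.
- *Within persons.* While the same informant is kept, b(i) is constant and cancels from Y(i,t) minus the participant's own mean.
- *Under Table 1.* Only parents and guardians supply scores, and most of this mixing does not arise.

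The article gives neither p nor d, so no size in score or SD units follows from it.

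**The case against.** The case against making much of this has four parts.

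1. *This is a condensed article.* Rules for keeping or replacing an informant commonly sit in the full protocol, and their absence here is not a fault. That stands for what is missing. It does not answer the contradiction, because both definitions are printed in this document.
2. *The analyses are mainly within-person.* The Background describes a within-individual design, and the Analysis plan separates within- from between-person effects. A stable rater offset falls in the between-person part. That stands, and it confines the problem to between-person comparisons of informant scores.
3. *The data affected are limited.* ADHD symptoms, impairment and irritability are also self-reported monthly, and the Analysis plan does not name informant scores as an outcome. That stands, and it lowers the importance of the point.
4. *The mixing follows from only one of the two rules.* That is true, but the article does not say which rule governs.

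A reader might go further and infer that the rater can switch at the transition itself, for example when the young person leaves home, so that a step between raters is read as symptom change. The documents do not support this. The participant names one informant at baseline, and nothing provides for a replacement. Nothing requires the same informant throughout either, so a change is conceivable, but it does not follow from this contradiction: a parent-only rule would equally allow one parent to take over from the other. The Background does say that "the main informant for ADHD diagnostic symptoms changes from parent (and teacher) to self", but this concerns clinical diagnosis and not the study's REDCap informant.

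A reader might also cite the Background's remark that "agreement between parents and young people with ADHD is only modest" as evidence of a rater effect, or as a reason to prefer parents. It compares parents with self-report, not one kind of informant with another, and it states no mean difference. The article uses it to argue for objective digital and cognitive markers, not for parent informants.

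**Conclusion.** The contradiction is real and the document is wrong as written: Table 1 and the two procedural sections cannot both be followed. If the procedures govern, the study would use informants whom Table 1 excludes, possibly including peers under 18, and between-person differences in informant BAARS-IV, impairment and ARI scores would mix rater type with severity.

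The under-18 element assumes that some chosen partners, friends or siblings are minors and that staff do not apply Table 1's age limit. The mixing assumes that rater types differ systematically in how they score. Both are plausible, but the documents quantify neither. Any step in SD units would rest wholly on an assumed rater gap and an assumed ICC, so none is offered.

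This is a point that should be fixed. It reaches the informant-report scales only and leaves self-report, passive and cognitive outcomes untouched.

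**What to change.** Reconcile Table 1 with Study procedures and Active app so that one informant definition and one age rule appear throughout, and align the invitation email with it. The definition should also settle whether a guardian who is not a relative may act as informant.

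If the wider list is kept:

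- state whether the 18-year limit applies to every informant, including partners and friends;
- record the informant's relationship to the participant at each REDCap report;
- include rater type as a covariate in analyses of informant scores;
- ask for the same informant throughout where possible.

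If the parent-or-guardian rule is kept, correct the two procedural sections to match.

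The cost is wording changes and, under the wider list, one REDCap item. Under the narrower rule, some participants may have no eligible informant and would contribute no informant scores. The relationship item is best added early, because a relationship not recorded at the time may be hard to recover later.
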